For vaccinated NH residents only, a survival analysis will be performed to investigate the proportion of deaths within the study follow-up and the time (in days) to a confirmed COVID-19 death since 14 days after being fully vaccinated (full dose regimen). The survival or censoring time (in days) is registered since 14 days after being fully vaccinated until first event (or censoring moment). A non-COVID-19 related death will be considered as a competing risk in the analysis. If the proportional hazard assumption holds, a stratified (by NH) Cox proportional hazards regression model will be used to model the cause-specific hazards between seropositive and seronegative residents. The latter will be included as a time-varying covariate. A history of self-reported SARS-COV-2 infections, a time-varying NH vaccination degree, province, age, gender, care profile, and presence of COVID-specific comorbidities will be

considered for model adjustment.

7. To assess the duration of SARS-CoV-2 specific antibody response (seroreversion/no antibody response) since 14 days after being fully vaccinated among NH residents and staff in Belgium.

The duration of SARS-CoV-2 specific antibody responses among NH residents and staff in Belgium will be modelled by means of an interval-censored survival analysis. Seroreversion will be defined as a negative rapid test result after at least one positive rapid test result or as two succeeding negative test results (implying the participant did not seroconvert after vaccination within two to four months). The time interval to seroreversion/no response is the time interval between 14 days after the (second) vaccination date (full dose regimen) and the first test moment of a negative test result after at least one positive rapid test or of the two succeeding negative rapid test results. As a sensitivity analysis, the event will also be defined as two succeeding negative rapid test results (whether or not after at least one positive rapid test result), if the rapid test result would turn out to be unstable.

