### **Tertiary objectives**

Although this study was not designed to assess vaccine effectiveness, end points will be compared between vaccinated and non-vaccinated participants, applying propensity score methods, if sufficient non-vaccinated participants occur in the random selected sample.

8. To assess the risk of getting SARS-CoV-2 infected between vaccinated and non-vaccinated (at last visit) residents/staff.

If a sufficient number of non-vaccinated participants are available in the sample, a survival analysis will be performed to investigate the time (in days) to a SARS-CoV-2 infection

since 14 days after being fully vaccinated between vaccinated and non-vaccinated participants. A participant is considered to have an event when the participant had a reported positive PCR test result (or a positive antigen rapid test, or a positive CT scan, or a positive saliva test in absence of a PCR test) during the baseline or one of the follow-up visits. The survival or censoring time (in days) is registered since 14 days after being fully vaccinated (or since 14 days after main (second) vaccination date in corresponding NH in case of non-vaccinated participants) until first event (or censoring moment).

If the proportional hazard assumption holds, a stratified (by NH) Cox proportional hazards regression model will be used to model the hazard of SARS-CoV-2 infection between staff and residents, and between vaccinated and non-vaccinated participants, adjusting for history of self-reported SARS-COV-2 infections, and a time-varying NH vaccination degree. Propensity score methods will be applied to reduce the effects of confounding. If insufficient non-vaccinated residents would be available in the cohort, the analysis will be performed for staff only.

9. To assess the proportion of confirmed COVID-19 deaths and non-COVID-19 related deaths and the time until death (within the study timeframe) between vaccinated and non-vaccinated residents.

If sufficient non-vaccinated residents would be available, a survival analysis will be performed to investigate the time (in days) to a confirmed COVID-19 death since 14 days after vaccination (or since 14 days after main (second) vaccination date in corresponding NH in case of non-vaccinated participants). A non-COVID-19 related death will be considered as a competing risk in the analysis.

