- Ik ben tijdens de crisis een individu met risico op COVID-19 geworden
- Ik werd geïnformeerd over het risico van ernstig ziek te worden op COVID-19
- Ik werd me bewust van het voorkomen van nieuwe, meer besmettelijke varianten van het coronavirus
- Anders : \_\_\_\_\_ (deelnemers krijgen een invulveld)
- Ik verkies niet te antwoorden

D . Wat is/zijn de redenen waarom u u later laat vaccineren? *(meerdere antwoordmogelijkheden)*

- Ik was afwezig tijdens de eerste vaccinatieronde in het WZC (ziekte/vakantie) en heb sindsdien niet meer de kans gehad om me te laten vaccineren
- Ik heb een chronische aandoening en vaccinatie werd op het moment van de eerste vaccinatieronde niet aanbevolen
- Ik was zwanger en een vaccinatie werd op het moment van de eerste vaccinatieronde niet aanbevolen

- Ik wens in de nabije toekomst zwanger te worden
- Ik ben aan het wachten op een specifiek vaccin
- Anders : \_\_\_\_ (deelnemers krijgen een invulveld)
- Ik verkies niet te antwoorden

E . Wat is de hoofdreden waarom u niet gevaccineerd wenst te worden tegen COVID-19?

- Ik ben bezorgd over onbekende toekomstige effecten van het vaccin
- Ik ben bezorgd over de bijwerkingen van het vaccin
- Ik vertrouw vaccins niet.
- Ik denk dat het onwaarschijnlijk is dat ik ernstig ziek zal worden van het coronavirus
- Ik vind dat de impact van het coronavirus wordt overdreven
- Ik denk dat het vaccin niet kan verhinderen dat ik besmet zal geraken met het virus
- Ik heb een aandoening waardoor het vaccin niet veilig is voor mij
- Ik ben reeds besmet geweest met COVID-19 dus ik heb geen vaccin nodig
- Ik ben bang van naalden
- Ik heb geen mensen in mijn omgeving die tot de risicogroep behoren
- Anders : \_\_\_\_\_ (deelnemers krijgen een invulveld)
- Ik verkies niet te antwoorden

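### Objectives 6 and 9 count a confirmed COVID-19 death after time zero without requiring the fatal infection to begin after it; in objective 9 this pulls the comparison modestly toward no difference

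*Protocol*

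**What the plan says.** **Objective 6** (Protocol section 3.2, secondary objectives) is restricted at the outset: "For vaccinated NH residents only, a survival analysis will be performed". The outcome is "the time (in days) to a confirmed COVID-19 death since 14 days after being fully vaccinated (full dose regimen"), and the clock is set by this sentence: "The survival or censoring time (in days) is registered since 14 days after being fully vaccinated until first event (or censoring moment"). The contrast is between seropositive and seronegative residents, and of serostatus the plan says "The latter will be included as a time-varying covariate". Earlier infection appears only in a list of variables to be considered for adjustment: "A history of self-reported SARS-COV-2 infections, a time-varying NH vaccination degree, province, age, gender, care profile, and presence of COVID-specific comorbidities will be" considered.

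**Objective 9** (tertiary objectives) compares vaccinated with non-vaccinated residents, if there are enough of the latter, "to investigate the time (in days) to a confirmed COVID-19 death since 14 days after vaccination". For non-vaccinated residents the clock starts 14 days after the home's main second vaccination date. History of self-reported infection is in the model, and propensity score methods are to be used.

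Both objectives treat non-COVID-19 death as a competing risk. Neither sets a condition on the date of the infection that led to death, and neither excludes or delays residents already infected at time zero.

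**The concern.** Starting the clock 14 days after full vaccination suits an infection endpoint, because an infection detected earlier falls outside the analysed time. Death is a later stage of the same infection. With the same start, a death inside the analysed time can come from an infection outside it. One resident can then be a COVID-19 death in objective 6 or 9 with no matching infection event in objective 5 or 8.

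The infection-history covariate does not repair this. It puts a resident infected a few days before time zero together with one who recovered months earlier. At stake are the vaccine mortality comparison in objective 9 and the serostatus mortality comparison in objective 6.

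**Working it through.** The protocol gives no figure for objectives 6 or 9 to reproduce. Section 2.5 sizes the study only for the precision of seroprevalence and cumulative incidence.

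**1. The rules side by side**

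| Objective | Event | Clock starts | Infection before the clock |
|---|---|---|---|
| 5, 8 | Positive test | 14 days after full vaccination (8, non-vaccinated: 14 days after the home's main second date) | Outside the analysed time |
| 6 | Confirmed COVID-19 death | 14 days after full vaccination | A later death counts |
| 9 | Confirmed COVID-19 death | 14 days after vaccination (non-vaccinated: as in 8) | A later death counts |

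**2. Where a death can be misattributed**

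- Objective 9, vaccinated: the infection began before protection is assumed, yet the death counts as a vaccinated death. This is a misattribution.
- Objective 9, non-vaccinated: the resident was also non-vaccinated when infected, so the group is correct.
- Objective 6: everyone is vaccinated, so vaccination status cannot be wrong. Under section 2.7.1 any IgM or IgG line counts as positive, so the infection itself can turn the test positive before death. Serostatus is read only every two months, so the last reading may also predate that. The direction is not determined.

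**3. Calendar**

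The campaign began on 5 January 2021 (table of changes). Table 1 marks the first blood collection in February 2021. With an assumed dose interval of 21 to 28 days, the earliest time zero is 5 January + 21 + 14 days = 9 February, or 5 January + 28 + 14 days = 16 February. This is the baseline month, so early deaths are partly observed and partly lost before enrolment.

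**4. Size in objective 9 (all inputs assumed)**

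The hazard of fatal infection is constant. Infection-to-death lag is gamma, shape 4, mean m = 14 or 21 days. Follow-up ends 300 days after time zero. The true death-rate ratio is r = 0.10 or 0.30. Before time zero, the vaccinated have f times the non-vaccinated rate of fatal infection, with f = 1 (no protection) or 0.5 (half).

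Let s be the share of non-vaccinated COVID-19 deaths that come from infections before time zero. Then:

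- apparent ratio = r(1 − s) + f·s = r + (f − r)·s
- pre-time-zero share of vaccinated deaths = f·s / [r(1 − s) + f·s]

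Observed from time zero, s = m/300: 14/300 = 4.7% or 21/300 = 7.0%.

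- r = 0.10, f = 0.5, m = 14: 0.10 + 0.40 × 0.047 = 0.119
- r = 0.10, f = 1, m = 21: 0.10 + 0.90 × 0.070 = 0.163
- r = 0.30, f = 0.5, m = 14: 0.30 + 0.20 × 0.047 = 0.309
- r = 0.30, f = 1, m = 21: 0.30 + 0.70 × 0.070 = 0.349

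The pre-time-zero share of vaccinated deaths runs from 7.5% (r = 0.30, f = 0.5, m = 14) to 43% (r = 0.10, f = 1, m = 21).

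Observed only from day 28, numerical integration gives s = 0.1% (m = 14) or 0.7% (m = 21). The largest apparent ratios are then 0.10 + 0.90 × 0.007 = 0.106 and 0.30 + 0.70 × 0.007 = 0.305. The vaccinated share falls to between 0.1% and 6.5%.

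The bias is toward no difference whenever f exceeds r. If the vaccine does nothing (r = f = 1), the apparent ratio is 1, so this mechanism cannot create a benefit.

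**The case against.** **The effect may be small.** Participants must consent and give a capillary sample (section 2.4.1), so residents who died before enrolment are not in the cohort and those dying of acute infection are unlikely to join it. This stands, and it is why the day-28 figures matter. It limits the size and does not make the event rule correct.

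**Partly handled already.** Objective 9 is tertiary and conditional on numbers. It uses propensity scores, adjusts for infection history, and sits under a statement that the study was not designed for vaccine effectiveness. That lowers the stakes. None of it separates an infection active at time zero from an old one.

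**A statistical analysis plan could settle it.** It could refine the event rule, and the baseline form already asks for the first positive-test date. It could not create missing data. On the resident follow-up form (appendix 6.3), death is a reason for not completing the form and only a category and date of death are asked there; the positive-test date is a later item. For a resident infected and dead between visits, that date is not secured.

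**A stronger reading.** A reader might infer that residents too ill to be vaccinated fill the non-vaccinated group and die, producing a large spurious vaccine benefit. Some residents may indeed be non-vaccinated because they were ill, but the documents support no size for this:

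- The form wording that suggests it, "Ik was afwezig tijdens de eerste vaccinatieronde in het WZC (ziekte/vakantie"), comes from the one-off staff questionnaire. It is asked of staff who expect to be vaccinated soon and does not name COVID-19. Objective 9 covers residents.
- It refers to the first round, whereas the non-vaccinated clock starts 14 days after the second. With an assumed 21 to 28 days between doses, time zero is 35 to 42 days after the first round. A resident acutely infected at that round who dies 14 to 28 days later dies 7 (35 − 28) to 28 (42 − 14) days before time zero and is never an event.
- The documents give no number of non-vaccinated residents.

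**Conclusion.** The concern holds in limited form. As written, both objectives count confirmed COVID-19 deaths from infections that began before time zero. In objective 9 the clear misattribution is on the vaccinated side and pulls toward no difference. In objective 6 no vaccination status can be wrong, and the effect on the serostatus comparison has no determined direction.

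The size is probably modest: a true ratio of 0.10 appears as 0.12 to 0.16, and 0.30 as 0.31 to 0.35, if residents are observed from time zero. With observation from day 28 the figures are at most 0.106 and 0.305. These rest on assumed lags, assumed protection before time zero and constant incidence. Incidence falling after the campaign would raise the shares and a later wave would lower them. The protocol gives no incidence curve, so a much larger share should not be inferred.

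**What to change.** In Protocol section 3.2, objectives 6 and 9:

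1. Count a confirmed COVID-19 death as the event only if the first positive test of that infection is dated on or after time zero.
2. Let a resident with a positive test in a fixed window before time zero (for example 28 days) enter the risk set only once that window has passed, and let no one enter before enrolment.
3. Tabulate deaths from earlier infections separately.

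In appendix 6.3, add to the death item of the resident follow-up form, in both languages, the date of the first positive test of the fatal infection.

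The cost is a short addition to each of two analyses, one more date to collect, and slightly fewer COVID-19 deaths analysed.

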#### **Secondary objectives**

1. To assess the seroprevalence according to vaccination status among NH residents and staff in Belgium at month 0 and at every follow-up visit in the cohort at month 2, 4, 6, 8 and 10.
2. To assess the risk of getting a SARS-CoV-2 infection since vaccination between:
  - Residents and staff
  - Seropositive and seronegative participants at all timepoints
  - Individuals with or without previous self-reported SARS-CoV-2 infections
  - Adjusted for the updated vaccination degree of NH at all timepoints
3. To assess the proportion of confirmed COVID-19 deaths and non-COVID-19 related deaths and the time until death since vaccination (within the study timeframe) between sero-positive and -negative participants for NH residents
4. To assess the duration of SARS-CoV-2 specific antibody responses (seroreversion/no antibody response) since vaccination among NH residents and staff in Belgium.

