## **2.7 Data Collection**

### **2.7.1 Collection of capillary blood samples and point-of-care test procedures**

The capillary blood samples will be obtained using a lancet to finger prick the middle finger and collect a 1-10 drops of capillary blood. A capillary blood drop will be transferred to the

specimen well of a point-of-care (POC) test (COVID-19 IgG/IgM Rapid Test Cassette, Orient Gene Biotech Co.) using a plastic dropper (delivered with COVID-19 IgG/IgM Rapid Test kit). Two drops (ca. 80 µl) of Orient Gene Biotech sample buffer will be immediately added to the buffer well, with avoidance of air bubbles. If the red colour does not move across the test window or if blood is still present in the specimen well after two minutes, one additional drop of sample buffer should be added into the buffer well. The result should be read in 10 minutes, positive test results may be visible as soon as 2 minutes. The result cannot be interpreted after 15 minutes.

The results of the COVID-19 IgG/IgM Rapid Test Cassette should be interpreted as following:

- **Negative:** The coloured line in the control region (C) changes from blue to red. No line appears in the test line region M or G.
- **Anti-COVID-19 IgM positive:** The coloured line in the control region (C) changes from blue to red and a line appears in the test line M.
- **Anti-COVID-19 IgG positive:** The coloured line in the control region (C) changes from blue to red and a line appears in the test line G.
- **Anti-COVID-19 IgG and IgM positive:** The coloured line in the control region (C) changes from blue to red and a line appears in the test line G and M.
- **Invalid test:** Control line is still completely or partially blue and fails to completely change from blue to red. Insufficient specimen sample or incorrect procedural techniques are the most likely reasons for control line failure. The test should be repeated using a new cassette.

For the study any positive result of IgM or IgG will be considered as a positive result. In case of an invalid test, the test is repeated. When it is still invalid it will be noted as such. Additionally, a few drops of capillary blood will be collected on Dried Blood Spot (DBS) collection cards for (semi-)quantitative analysis of vaccine-induced/infection-induced anti-SARS-CoV-2- specific antibodies as a part of the sub-study performed by Ghent University (details are provided in appendix 6.4).

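### Objective 6 does not exclude rapid tests taken after the onset of the fatal infection, so some COVID-19 deaths in residents who were seronegative when infected can be counted as seropositive

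*Protocol*

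**What the plan says.** The objective in section 2.1 is to compare deaths and "the time until death since vaccination (within the study timeframe) between sero-positive and -negative participants for NH residents".

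For objective 6, section 3.2 specifies:
- **Endpoint and origin:** "the time (in days) to a confirmed COVID-19 death since 14 days after being fully vaccinated". Follow-up runs to that event or to censoring.
- **Competing risk:** "A non-COVID-19 related death will be considered as a competing risk in the analysis". Infection is neither an event nor a censoring point.
- **Model:** a Cox model stratified by nursing home will "model the cause-specific hazards between seropositive and seronegative residents. The latter will be included as a time-varying covariate".
- **Adjustment:** self-reported infection history is among the covariates to be considered. In that list, only the vaccination degree of the home is called time-varying.

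On the exposure, section 2.7.1 says: "For the study any positive result of IgM or IgG will be considered as a positive result". The rule does not separate vaccine antibodies from those raised by a past or current infection.

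Rounds are about 60 days apart (section 2.4). Section 4.3 gives the rapid test a sensitivity of 92.9% and accepts that results will be missing for hospitalised residents.

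**The concern.** The comparison is informative about protection only if serostatus is the status the resident had when infected. Here the endpoint comes after infection. A round can fall between the antibody response to an infection and the death from it, and the exposure is then a product of the disease that causes the event.

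Example: a resident is seronegative and infected in March, has a new IgM or IgG line at the April round, and dies of that infection a week later. Read plainly, the plan attributes this death to the seropositive group.

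Reassignment of this kind goes one way. It takes COVID-19 deaths from the seronegative group and adds them to the seropositive group, so it pushes the hazard ratio upwards. A real association with fewer deaths would look weaker, and no association could look like harm. Objective 5 uses the same time-varying serostatus, but its follow-up ends at the first reported infection.

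**Working it through.** **Plan's own figure.** Objective 6 has no event count, effect size or power. The calculation in section 2.5 serves the primary objectives. It reproduces (381 x 2.68 = 1021.1, rounded up to 1022; 69 x 44 = 3036) but does not bear on this point.

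**Inputs from the protocol.** Round interval 60 days (2.4); test sensitivity 0.929 (4.3).

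**Assumed inputs, none of them in the protocol.** Mean infection-to-death time 15-40 days (middle 21-28); mean infection-to-seroconversion time 8-16 days (middle 12); chance that an ill resident is tested at the round 0.3-1.0 (middle 0.6); seronegative share of person-time s = 0.10-0.40 (middle 0.20); true hazard ratio 0.30, 0.50 or 1.00. The last test result is carried forward.

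**Step 1: share of seronegative COVID-19 deaths moved, m.** By hand, with fixed times:

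m ≈ (days to death − days to seroconversion) / 60 x sensitivity x chance of being tested

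- 21 and 12 days: 9/60 x 0.929 x 0.6 = 0.084
- 28 and 12 days: 16/60 x 0.929 x 0.6 = 0.149

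A simulation that lets these times vary between residents (400,000 fatal infections per scenario) gives 0.092 and 0.152. Over the whole assumed grid m runs from 0.012 to 0.482.

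**Step 2: effect on the hazard ratio.** Let the seronegative death rate be 1 and total person-time be 1. Seronegative deaths number s and seropositive deaths HR x (1 − s). Moving m x s deaths, and ignoring the short person-time that moves with them, gives

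HR seen = [HR + m x s/(1 − s)] / (1 − m)

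With s = 0.20, s/(1 − s) = 0.25. For m = 0.092 and HR = 0.30: (0.30 + 0.023)/0.908 = 0.36. For m = 0.152: (0.30 + 0.038)/0.848 = 0.40.

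| m | True 0.30 | True 0.50 | True 1.00 |
|---|---|---|---|
| 0.012 (lowest) | 0.31 | 0.51 | 1.02 |
| 0.092 | 0.36 | 0.58 | 1.13 |
| 0.152 | 0.40 | 0.63 | 1.22 |
| 0.482 (highest) | 0.81 | 1.20 | 2.16 |

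At the highest m, varying s from 0.10 to 0.40 takes a true 0.30 to between 0.68 and 1.20. If serostatus is held at its pre-infection value, m = 0 and this bias disappears.

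**Step 3: set against precision.** Assume, for illustration, 20 confirmed COVID-19 deaths, a true HR of 0.30 and s = 0.20. The seronegative share of deaths is 0.20/(0.20 + 0.80 x 0.30) = 0.455, about 9 deaths, leaving about 11 seropositive. Moving 9-15% of 9 is about one death. The standard error of log HR is about √(1/9.1 + 1/10.9) = 0.45. The shift is ln(0.36/0.30) = 0.18 to ln(0.40/0.30) = 0.29, so less than one standard error.

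**The case against.** **The text is silent rather than explicit.** A reader might infer that the plan states that serostatus keeps updating after infection. It does not: it says only that the covariate is time-varying, with no lag, carry-forward or post-infection rule. Such coding rules are often left to a statistical analysis plan, and none is at hand. This stands as a limit on the wording: the protocol does not exclude such tests. It does not remove the point, because the protocol itself fixes the death endpoint, the follow-up and the form of the covariate, and their plain combination produces the bias.

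**The size is easily overstated.** A reader might infer that most seronegative deaths move, or that the comparison is reversed. The documents do not support that. With rounds 60 days apart, only deaths with a round between seroconversion and death can move, and section 4.3 expects missing results in hospitalised residents. If every ill resident were tested with perfect sensitivity, 21 days to death and 10 to seroconversion would give 11/60 = 18% and take 0.30 to 0.42. That is too high as a central value, given what section 4.3 says about both.

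**Adjustment for infection history might help.** That covariate is only to be considered, its timing is not defined, and it cannot restore the pre-infection serostatus. If it were updated, the fatal infection itself could count as history.

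**A careless remedy would bring its own bias.** This is right. Resetting serostatus only for residents who die makes exposure depend on the outcome. Freezing it for good at first infection would leave antibody-positive survivors in the seronegative group.

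**Conclusion.** The point holds as a flaw in one secondary model. As written, objective 6 lets antibodies raised by the fatal infection define the exposure, and the resulting bias runs against the seropositive group. That direction follows from the protocol; the size does not. About 9-15% of seronegative COVID-19 deaths moved is a reasonable middle value. It rests on assumed times to death and seroconversion and a 60% chance of testing while ill; the hazard ratios also assume 20% seronegative person-time. The share is near zero if death is quick or ill residents are rarely tested, and much larger if death is slow and testing complete. With few deaths, the shift may be hidden by sampling error. The primary objectives are not touched, and objective 5 is not exposed in this way. The rule should be fixed before analysis, because it is cheap and the bias has a known direction.

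**What to change.** Add to section 3.2, objective 6, a rule that applies to every resident regardless of outcome:

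- A rapid test taken on or after a dated positive PCR, antigen or CT result, or on or after a reported symptom onset that meets the case definition in section 2.7.2, does not update serostatus during that infection episode.
- The last rapid test before that date is carried forward through the next scheduled round. Updating resumes at the round after that.
- The same rule applies to infection history, so that the current episode does not count as history.
- No rule may apply only to residents who die.
- The continuously updated version is kept as a sensitivity analysis.

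The cost is a few sentences and a programming rule. No new data are needed: the resident follow-up form in Appendix 6.3, completed in the week of the test, already asks for the dates of positive tests and of symptom onset.

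The downsides should be stated. Some person-time carries an older serostatus value, for up to about 120 days after the infection date (two round intervals). The infection dates are approximate and partly proxy-reported. Some misclassification will remain, for example when no symptoms are reported and the first positive test comes after the round, or when death comes after updating has resumed, at least about 60 days from onset.
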